To date, evidence about direct access to physiotherapy comes from observational studies only. These have suggested that direct access may reduce GP workload [19] with estimates of a 20 % reduction in multiple GP consultations [20]. An evaluation in the Netherlands reported that in the first 12 months of direct access, patients referring themselves accounted for 22–28 % of all physiotherapy referrals [14, 21]. Reported patient benefits of direct access are greater freedom of choice and improved access to musculoskeletal care [13, 14, 19, 22], since direct access allows the patient to opt for physiotherapy when they are in most need. There are also some suggested cost-benefits, with GP referral costing £133 an episode and an episode of care through direct access costing £100 [23].

A global review of direct access to physiotherapy has identified professional legislation, the medical profession, politicians and policy makers as both barriers to and facilitators of direct access [24]. A European-focused review of direct access services concluded that clinicians, managers and service funders need high quality trial data on both clinical and cost-effectiveness to guide decisions on the best models of care [25]. In addition, an independent evaluation of the observational UK Department of Health pilots of direct access to physiotherapy [13] concluded that robust evidence of the impact on clinical outcomes, work loss and costs are lacking due to important flaws in observational study designs and that a randomized controlled trial (RCT) comparing areas that do and do not offer direct access is required to provide robust evidence about direct access [26].

The most appropriate design for a RCT to evaluate direct access is a non-inferiority cluster RCT that compares the clinical and cost-effectiveness of the additional offer of direct access to physiotherapy versus continuing with usual GP-led care alone for patients with musculoskeletal conditions in primary care. However, given that this involves developing a new direct access service, it is important to conduct feasibility and pilot work first in order to fully inform a future main trial.

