### Participant identification and recruitment

Following randomisation of GP practices, potentially eligible participants will be identified through one of three methods.

Method 1: Patients consulting GP practices with a musculoskeletal problem will have a musculoskeletal Read code^1^ (entered by GPs or nurse practitioners) entered into their computerised medical record. A member of the GP practice team, or CRN staff, will download the details of patients with these Read codes twice weekly checking for exclusion criteria and then forward these details to a CRN administrator. GPs will be able to exclude any patients they perceive as being particularly vulnerable and unsuitable to approach for involvement in research by using a dedicated exclusion code set up for the study.

Method 2: In addition, for those GP practices randomised to also offer direct access to physiotherapy, patients who self-refer to physiotherapy will be identified when they forward a completed self-referral form to the physiotherapy service or telephone the physiotherapy administrator for help in completing a form. As in method 1 the details of identified patients will be forwarded to a CRN administrator.

Method 3: Patients referred by GPs or practice nurses to the physiotherapy service, but not identified in method 1 due to an absence of an appropriate Read code in the computerised medical records, will be identified from the physiotherapy administration database. A physiotherapy administrator will download the details of all patients referred from the participating GP practices twice weekly and forward these details to a CRN administrator. Duplication checks will ensure that eligible patients are not invited to take part in the research more than once.

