Baseline risk of persistent problems	STarT Musc tool (draft tool developed at Keele University to identify patients’ risk of persistent pain and disability)	✓	✘	✘	✘
Pain location	Body manikin	✓	✘	✘	✘
Pain duration	Single question about duration of pain	✓	✘	✘	✘
Comorbidities	Single question	✓	✘	✘	✘
Economic outcomes					
Further health care utilisation	Consultations, investigations, procedures, admissions, over-the-counter medications	✘	✘	✓	✓
Work absence	Single question	✓	✓	✓	✓
Presenteeism	Single work performance question	✓	✓	✓	✓
Willingness to pay	Three willingness to pay questions	✘	✘	✘	✓

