#### Analyses of clinical outcomes

Analyses will be conducted for the clinical outcomes, but this will be treated as exploratory and will be mainly descriptive. A baseline table (descriptive statistics and frequencies) will compare the demographic and clinical characteristics (gender, age, education, employment status, pain interference with performance at work, type of accommodation, health literacy, physical health (SF-36v2 PCS) and mental health (SF-36v2 MCS), pain location, physical function, pain duration, baseline risk of persistent problems, comorbidities, pain self-efficacy, understanding of the condition, experience of care and convenience and accessibility of service) between the two arms. Since the baseline assessment for the clinical characteristics will be completed, for many patients, after their initial consultation about their musculoskeletal problem, there could be implications on evaluation and interpretation of these measures as they may not be ‘true baseline’ but rather possible ‘outcomes’ at the first time-point. All continuous variables will be summarised using mean, standard deviation, median and interquartile range as appropriate. The frequency and percentages of observed levels will be reported for all categorical measures.

As this is a pilot trial, no emphasis will be put on the *p* values for any inferential statistical tests conducted. A mixed effect model, which allows all available data at all the four time-points to be used and account for missing data and clustering effect, will be used to estimate a two-sided 95 % CI to show a credible range for the true difference in the SF-36v2 PCS subscale between intervention and the control arms. The model will be adjusted for key patient-level baseline characteristics (age, area level deprivation and widespread pain (from manikin data)) and a random effect for the GP practices and will include a treatment-by-time interaction to obtain the estimates of treatment effect (and 95% CI) at each follow-up visit (2, 6 and 12 months). Analyses of the secondary outcomes will be performed similarly.

Further analysis will descriptively compare the baseline characteristics and key clinical outcomes between the participants referred to physiotherapy in the control practices with participants self-referring in the intervention practices. We will also compare the self-referrers with those that do not self-refer within the intervention group.

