#### Health economic analysis

The economic analysis will be exploratory, with the aim to inform the design of a full cost-utility analysis alongside a future main trial. A cost-consequence analysis will be reported, describing all the important results relating to costs and consequences for direct access to physiotherapy and usual care arms of the trial. Results will be presented from a health service perspective and a broader societal perspective taking into account patient-incurred costs and productivity losses. An exploratory willingness to pay (WTP) study [37] will also be conducted to assess the use of this methodology to measure broader benefits of direct access.

Data on costs will be sought from all participants and from a broad perspective, taking into account healthcare, patient and societal costs. Healthcare resource used will be collected using self-completed questionnaires at 6 and 12 months, with a recall period of 6 months in each. Questions will ask patients to recall GP consultations, visits to healthcare professionals, outpatient appointments, investigations or treatments and inpatient stays related to the index condition. Participants will be asked to distinguish between NHS and private practice visits. Resource used for the direct access pathway will be directly recorded and costs attached, staff time (taking into account any increased referrals to physiotherapy), materials (posters, flyers, referral forms) and training sessions. GP medical record review of all participants will provide data on relevant prescribed medications for all musculoskeletal problems. In addition, information on costs borne by the patient (e.g. over-the-counter medicines, devices) will be collected via the self-complete questionnaires. Productivity costs will take into account both absenteeism and presenteeism and will utilise self-report data on employment status, occupation and time off work and reduced productivity at work (presenteeism). As this is a pilot trial, the suitability of questions for collecting cost data directly from patients can be assessed, in order to ensure effective resource use and that cost data collection systems are established for a larger trial.

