## Results and discussion

The STEMS pilot trial will investigate the feasibility of a future large trial to compare the clinical and cost-effectiveness of the additional offer of direct access to physiotherapy versus continuing with usual GP-led primary care alone for adults with common musculoskeletal problems. It is essential that changes to service provision and delivery are supported by research evidence and arguable that research about how to improve the delivery of health care is just as important in improving the health of patients with musculoskeletal conditions as the testing of new drugs or therapeutic approaches.

Previous research into direct access to physiotherapy has been limited to observational studies with the inherent limitations of observational designs. No previous trials have been conducted into direct access to physiotherapy for patients with musculoskeletal problems and this pilot trial will inform a main trial to fill this evidence gap and meet the calls to provide robust trial evidence of the impact on clinical outcomes, work loss and costs in a trial comparing areas that do and do not offer direct access [26] and to provide clinicians and service commissioners with the high quality trial data they need to guide decisions on the best models of care [25]. Direct access will be deemed to be the preferred model if it is not inferior in terms of patients’ physical health (on the SF-36v2 PCS—the main trial primary outcome) and is associated with benefits such as shorter waiting times, greater satisfaction, improved work outcomes and greater cost-effectiveness. Direct access may prove to be more cost-effective if it reduces other health service consultations and prescriptions, or improves quality of life or less cost-effective if it involves additional physiotherapy consultations with no reduction in GP consultations or prescriptions or improvements in quality of life

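### The stated cost window reaches back only to about baseline, so it misses the index GP or nurse consultation that true self-referrers do not have, and tilts the cost comparison modestly against direct access

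*Protocol article*

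**What the plan says.** All places are in the protocol article.

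- **Source and window of resource use.** Health economic analysis: "Healthcare resource used will be collected using self-completed questionnaires at 6 and 12 months, with a recall period of 6 months in each". The items asked are these: "Questions will ask patients to recall GP consultations, visits to healthcare professionals, outpatient appointments, investigations or treatments and inpatient stays related to the index condition".
- **Schedule.** In Table 2 (Outcome measures), the health care utilisation row, "Consultations, investigations, procedures, admissions, over-the-counter medications", is ticked at 6 and 12 months and crossed at baseline and 2 months.
- **Entry to the evaluation.** Participant identification and recruitment, Method 1: "Patients consulting GP practices with a musculoskeletal problem will have a musculoskeletal Read code". Those codes are downloaded twice weekly, and the baseline pack is then posted. Method 3 picks up GP or nurse referrals from the physiotherapy database. Method 2 picks up self-referrers when they submit the form or telephone for help with it.
- **Order of events.** Analyses of clinical outcomes accepts that the baseline clinical assessment "will be completed, for many patients, after their initial consultation about their musculoskeletal problem". The point is made for clinical measures and not carried over to costs.
- **Direct-access costs.** Health economic analysis: "Resource used for the direct access pathway will be directly recorded and costs attached". Staff time, materials and training are listed.
- **Records.** The same section assigns record review to prescribed medications. Later it names record reviews, without restriction, as a source of cost data. The recruitment section says that consent covers review of healthcare use.

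**The concern.** The Results and discussion section sets out how the economic case could be made: "Direct access may prove to be more cost-effective if it reduces other health service consultations and prescriptions". For a patient who goes straight to physiotherapy, the first consultation that could be saved is the index GP or nurse visit. If the costing window opens after that visit, it is missing for everyone who had it. The comparison then cannot show that true self-referrers did without it, while the intervention arm still carries the cost of running the pathway.

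An early estimate of costs in both groups is one of the research objectives, and the pilot is also meant to establish cost collection for the larger trial. A rule that leans one way could be carried forward.

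**Working it through.** **1. Timing.** For a Method 1 participant the order is: consultation and Read code, twice-weekly download, posting of the pack, return of the baseline questionnaire. Non-responders get a reminder at 2 weeks and a repeat pack 2 weeks after that. Baseline therefore follows the index consultation by some days to more than 4 weeks. The 6-month questionnaire looks back 6 months, to about baseline, and the 12-month questionnaire looks back to month 6. Neither reaches the index consultation, and a late 6-month return moves the window further from it. Method 3 and recommended self-referral participants are in the same position, since a GP or nurse contact came first. A true self-referrer is identified at self-referral, so the first physiotherapy visit normally falls inside the window.

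The start at baseline is inferred from the recall period. No section states a costing start date.

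**2. Form of the bias.** Let C be the unit cost of an index GP or nurse consultation and s the share of intervention participants who are true self-referrers.

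- Omitted per control participant: C
- Omitted per intervention participant: C × (1 − s)
- Recorded difference (intervention minus control) = full difference + C × s

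The shift is C for each true self-referrer, averaged over the arm.

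**3. Participants.** Sample size section: 100 per month × 0.80 eligible × 0.50 consenting × 4 practices × 6 months = 960, which reproduces the stated figure; 960 × 0.80 = 768 also matches. Equal arms are assumed: 960 / 2 = 480.

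**4. Size of s.** Inputs: r = 20–25% of patients under usual GP-led care referred to physiotherapy (Description of intervention and control arms); q = 20%, the minimum share of intervention-practice physiotherapy caseload to come through direct access (Feasibility of direct access). Assumptions: the same r applies in the intervention practices, take-up of the evaluation is equal across pathways, and every direct-access patient is a true self-referrer. The last makes s a maximum at this q, because recommended self-referrers count towards the 20% but have had the GP or nurse contact.

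Direct-access patients per GP consulter: D = r × q / (1 − q). Share of the arm: s = D / (1 + D).

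| r | D | s | true self-referrers of 480 |
|---|---|---|---|
| 20% | 0.20 × 0.25 = 0.0500 | 0.0500 / 1.0500 = 4.8% | 22.9 |
| 25% | 0.25 × 0.25 = 0.0625 | 0.0625 / 1.0625 = 5.9% | 28.2 |

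A larger s needs uptake above the minimum. For s = 10%, D = 0.10 / 0.90 = 0.111, and direct access would have to be 0.111 / (0.111 + r) = 31–36% of caseload.

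**5. Illustration in money.** The article gives no cost for a GP visit. The Background cites an observational comparison "with GP referral costing £133 an episode and an episode of care through direct access costing £100", a gap of £133 − £100 = £33. That is a whole-episode difference. Taking C = £33 purely as an assumption, C × s = £33 × 0.0476 = £1.57 to £33 × 0.0588 = £1.94 per intervention participant.

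**The case against.** The strongest reply is that records could fill the gap. Consent covers review of healthcare use, record reviews are named generally as a source of cost data, and GP consultations are counted as a process outcome. A reader might infer from the 6- and 12-month recalls that the index visit is never costed, or that records are used for prescriptions only. The article does not support either statement. What stands is narrower: the only costing use specified for records is medications, the process counts are anonymised and carry no cost, and no section says that records will supply the visit. Nor is this only detail left to a fuller document, because the article fixes source, time-points and recall length, and that combination excludes the visit.

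A second reply is that adding the visit to everyone except true self-referrers creates a saving by definition of entry. This does not succeed as an argument for leaving it out, since the visits to be added actually took place and used resources. It does limit interpretation. The Background says that only 30–40% of people with musculoskeletal problems consult their GP and that funders fear excess demand, and the bias section accepts that self-referrers may differ from GP consulters. A true self-referral is therefore not automatically an avoided consultation.

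Third, the economic analysis is exploratory and mainly descriptive, sensitivity analyses are planned, and none of the stated thresholds (40% recruitment, 70% retention at 6 months, 20% direct access) uses cost. That stands, and it lowers the severity.

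**Conclusion.** The point holds in a limited form. Followed as written, the costing rule does not capture the index GP or nurse consultation of Method 1, Method 3 and recommended self-referral participants. True self-referrers have no such consultation, and direct-access running costs are recorded directly, so the recorded cost difference is tilted against direct access.

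The effect is modest: at most about 23–28 people of 480, or 4.8–5.9% of the intervention arm, at the 20% caseload minimum. It is smaller if some direct access is recommended self-referral, and larger only if uptake exceeds the minimum. A reader might expect true self-referral shares of 10–25%, but the article's own figures do not give these at that minimum.

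The result rests on equal arms, equal take-up across pathways, GP referral of 20–25% in the intervention practices and a cost window starting at about baseline. Severity is moderate: no feasibility decision turns on it, but early cost estimates are an objective and the method is meant to serve the main trial.

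**What to change.** In the Health economic analysis section:

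1. Start each participant's cost window at the index contact: the GP or nurse consultation, or the self-referral date for true self-referrers.
2. In both arms, add the index GP or nurse consultation that actually occurred, taken from the medical record or the recorded pathway, at the unit cost already planned.
3. Extract prescriptions from the same date.
4. Report the cost comparison with and without the index contact as a sensitivity analysis, and note that true self-referrers might not otherwise have consulted.

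Because step 2 may rely on the recorded pathway, the two self-referral labels need one definition: the footnotes to Table 1 attach them the opposite way round from the Feasibility of direct access section.

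The cost is a wording change and a little more record extraction or, if the pathway alone is used, the assumption of a standard-length consultation. No new questionnaire or visit is needed.

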## Background

Musculoskeletal problems are common and costly and increase with age. Musculoskeletal conditions account for up to 30 % of general practitioner (GP) consultations [1], and yet it is estimated that only between 30–40 % of individuals with musculoskeletal problems consult their GP [2–4]. The Global Burden of Disease Study shows that musculoskeletal conditions are a major cause of chronic disability worldwide and have increased markedly in the last decade [5]. Given the ageing population and the increasing impact of these common painful conditions, the demand for musculoskeletal healthcare is set to rise and health care delivery systems will need to develop a ‘coherent policy for dealing with musculoskeletal disorders’ [5]. Best evidence for many of these musculoskeletal conditions recommends treatments such as advice, education, exercise, manual therapy and acupuncture [1, 6, 7]. Such treatments are cost-effective [8] and are those that professionals such as physiotherapists are equipped to deliver. Early physiotherapy intervention for musculoskeletal problems reduces sick leave and helps prevent acute problems becoming chronic [1, 9–12]. However, for most patients in the UK, access to National Health Service (NHS) physiotherapy is controlled through GP referral.

Direct access to physiotherapy is a system of access in which ‘patients are able to refer themselves to a physiotherapist directly without having to see anyone else first or without being told to refer themselves by a health professional’ [13]. Although direct access is well established in private practice in the UK and in other countries including Australia, the Netherlands, some states within the USA and in Scotland [14–17], uptake in the NHS in England has been very limited. Funders of physiotherapy services express concerns about creating excessive demand and associated costs and where direct access services have been established at least one in England has been stopped due to funding being withdrawn [18].

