All patients will be asked to complete the 5-level version of the EuroQoL-5D (EQ-5D) questionnaire at baseline, 6 months and 12 months in order for the quality-adjusted life years (QALYs) over the 12-month time period to be calculated for each participant. The QALYs combine information on health-related quality of life and survival.

Resource use will be multiplied by unit costs obtained from standard sources (NHS Reference Costs, British National Formulary, Unit Costs of Health and Social Care) and healthcare providers. Due to the lack of nationally representative unit cost estimates for private healthcare, this care will be costed as the NHS equivalent in the base case. Patient reported costs for over-the-counter treatments will be used. Productivity costs will be calculated using data collected on employment status at every time-point and days off work due to their musculoskeletal problem. For those in paid employment, information on occupation and the nature of their employment (full time or part time) will be requested. The average wage for each respondent will be identified using UK Standard Occupational Classification coding and annual earnings data for each job type. The analysis will use the human capital approach, and the self-reported days of absence will be multiplied by the respondent-specific wage rate. The human capital approach assumes that the value of lost work is equal to the amount of resources an individual would have been paid to do that work and values productivity losses as a result of morbidity (or mortality) by measuring time lost from work and multiplying this with the gross wage of the person. Responses to the EQ-5D questionnaire at baseline and 6 and 12 months will be used to calculate QALYs for each participant using the area under the curve method.

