As this is a pilot trial this will be an exploratory analysis, with the aim to inform the cost data collection and analysis of a future main larger trial. We will test our methods of collecting cost data, from patient questionnaires and medical record reviews and assess the completeness of the data collected. A cost-consequence analysis will be reported, describing all the important results relating to costs and consequences. Analyses will be mainly descriptive, and all costs and outcomes will be summarised using means and 95 % confidence intervals. The data for costs are likely to have a skewed distribution; therefore, the plan is to explore the nature of the distribution of costs. If the data is not normally distributed, a non-parametric comparison of means (e.g. bootstrapping) will be undertaken.

The base case cost analysis will adopt a NHS and personal social services (PSS) perspective. A broader costing perspective will be considered in a sensitivity analysis, taking into account NHS/PSS costs, patients’ personal expenditure and costs associated with work loss. The robustness of the results will be explored using sensitivity analysis and will explore uncertainties in the trial based data and any assumptions made in the base case analysis.

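### Private healthcare is priced into the base case, although the base case is defined as an NHS and personal social services perspective

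*Protocol article*

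**What the plan says.** All the relevant statements are in the protocol article's Health economic analysis section.

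- **Unit costs.** There are no nationally representative prices for private care, so "this care will be costed as the NHS equivalent in the base case".
- **Perspective.** "The base case cost analysis will adopt a NHS and personal social services (PSS) perspective".
- **Where other costs go.** "A broader costing perspective will be considered in a sensitivity analysis, taking into account NHS/PSS costs, patients’ personal expenditure and costs associated with work loss".
- **Reporting.** "Results will be presented from a health service perspective and a broader societal perspective taking into account patient-incurred costs and productivity losses".
- **Data.** "Participants will be asked to distinguish between NHS and private practice visits".

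Nowhere does the article say that private visits are left out of the NHS/PSS total.

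**The concern.** A costing perspective fixes whose costs are counted. A unit price fixes only how much each item counts for. Giving a private visit an NHS price does not make it an NHS cost, so the unit-cost rule and the perspective rule disagree about what the base case contains.

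This matters because the trial tests a new NHS route into physiotherapy, and the Background notes that "direct access is well established in private practice in the UK". Some private use among participants is therefore plausible, and the intervention might change it. If it does, a base case that includes private visits credits or charges the NHS for care it never bought. An early estimate of costs in both arms is one of the research objectives, and the economic work is intended to shape the main trial's cost-utility analysis. A badly fixed base-case rule could be carried forward.

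**Working it through.** The protocol states no figure to reproduce here. The check compares the two rules and then follows the consequence algebraically.

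**Step 1: the two rules side by side.**

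| Item | Unit-cost rule | Perspective rule |
|---|---|---|
| Private visits | Counted in the base case at NHS-equivalent price | Not NHS/PSS-funded, so outside the base case |
| Patients' own spending | Not assigned to a perspective | Broader sensitivity analysis only |

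The broader perspective is itself labelled a sensitivity analysis. The only cost base case the section defines is therefore the NHS/PSS one.

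**Step 2: effect on the total.** For each arm let *N* be the mean NHS/PSS-funded cost, *v* the mean number of private visits (or episodes) per participant and *c* the NHS-equivalent price of each.

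- Total as written: *N* + *c·v*
- NHS/PSS total: *N*
- Overstatement: *c* for each private visit

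**Step 3: effect on the difference between arms** (intervention minus control).

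- As written: (*N*_I − *N*_C) + *c*(*v*_I − *v*_C)
- NHS/PSS only: *N*_I − *N*_C
- Distortion: *c*(*v*_I − *v*_C)

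The distortion is zero if private use is equal in the two arms. It favours direct access if private use is lower in the intervention arm, and counts against it if private use is higher there.

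**Step 4: illustration for one replaced episode.** Suppose one private episode in the control arm corresponds to one NHS direct access episode in the intervention arm, all else equal. The Background gives £100 for a direct access episode and £133 for a GP-referred one. The protocol gives no NHS-equivalent value for a private episode, so *c* is assumed to lie between £50 and £150.

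| Assumed *c* | As written (100 − *c*) | Change in NHS cost (100 − 0) | Distortion (−*c*) |
|---|---|---|---|
| £50 | +£50 | +£100 | −£50 |
| £100 | £0 | +£100 | −£100 |
| £133 | −£33 | +£100 | −£133 |
| £150 | −£50 | +£100 | −£150 |

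**Step 5: scale per participant.** For each percentage point by which private episodes differ between arms, the mean cost difference moves by 0.01 × *c*. That is 0.01 × £50 = £0.50 up to 0.01 × £150 = £1.50. How many percentage points apply cannot be derived from the protocol.

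**The case against.** The best defence is that the unit-cost paragraph sets prices for every perspective at once. Its neighbouring sentences cover over-the-counter treatments and lost productivity, neither of which belongs to an NHS/PSS base case. Base case in that sentence may then mean only the default price for private care, with other prices tried in sensitivity analysis. This may well have been the intention. But the article does not say so, and it uses the same term shortly afterwards for the NHS/PSS analysis. An analyst could follow either meaning, so the sentences still need reconciling.

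Other mitigating points stand. The economic analysis is exploratory and mainly descriptive. The stated success thresholds concern recruitment, retention and direct access uptake, not cost. NHS physiotherapy consultations, referrals, staffing and waiting times are reported in their own right, so extra NHS demand would remain visible. Sensitivity analysis of base-case assumptions is promised in general terms, although private care is not named.

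A reader might also infer that control patients go straight to private physiotherapy and so load the control arm with private costs. The recruitment methods do not support this. Control participants are identified through a musculoskeletal Read code at the GP practice or a GP or nurse referral to NHS physiotherapy. Someone who bypasses both for private care is not in the control arm. What remains is private care used by people who were recruited through those routes, and the protocol does not say which arm would use more of it.

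**Conclusion.** The concern holds as an inconsistency between two stated rules. Taken literally, the plan counts care that the NHS/PSS does not fund in an NHS/PSS total, and overstates that total by the NHS-equivalent price of each private visit. This assumes that visits recorded as private are not paid for by the NHS or PSS.

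The distortion of the difference between arms is *c*(*v*_I − *v*_C). Its size and sign are unknown, because the protocol gives neither a rate of private use nor a price. What can be said is conditional: if NHS direct access replaces private care among participants, direct access will look cheaper to the NHS than it is.

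Two stronger conclusions are tempting but unsupported. One is that the base case will necessarily show a false NHS saving: a replaced episode of equal value shows no difference, which conceals a cost increase but is not a saving. The other is that the distortion is large relative to any real effect of the pathway, which no figure in the protocol can establish.

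This should be fixed because the costing rules are meant to inform the main trial. It does not threaten the pilot's feasibility conclusions.

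**What to change.** Change the Health economic analysis section in two places:

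1. State that visits recorded as private are excluded from the NHS/PSS base case.
2. State that they are counted in the broader-perspective sensitivity analysis, where the NHS-equivalent unit cost is used as an acknowledged approximation because representative private prices are lacking. Name private visits explicitly among the items in that perspective.

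The cost is about two sentences. No new data are needed, because the questionnaire already separates NHS from private visits. The downside is that the base-case cost difference may look less favourable to direct access, and the broader analysis will still value private care at something other than what was actually paid.
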